# STATISTICAL CONSIDERATIONS

- 1. Power Calculations

A sample size of 15 Type I, 45 Type II, and 40 Type III SMA cases provides 83% power for the primary outcome of Modified Hammersmith Functional Motor Scale using an elastic net multivariate regression analysis of Modified Hammersmith Functional Motor Scale on composite biomarker sets, at level 0.05, assuming a correlation between observed and theoretical outcomes of 0.75. This power calculation also assumes that 10% of analytes are true biomarkers, a variance of 0.2 for all analytes, with 100 analytes profiled. The power estimate is based on an average of 100 simulated datasets using data available from the original Hammersmith Scale.

The power to detect a mean fold change (MFC) of 1.3 in the key secondary outcome of SMA type, under the same assumptions as above, is 89% for univariate analysis of variance (ANOVA), when the false discovery rate (FDR) is controlled at level 0.10. For multivariate PAM analysis (Prediction Analysis of microarrays), power is 83% to detect a multivariate biomarker set with MFC of 1.2, when the theoretic prediction accuracy is 61%. These power calculations assume monotone identical differences between SMA types, and are based on an average of 100 simulated datasets for ANOVA and 1000 for PAM.

Additionally, the sample size of 100 SMA cases and 20 controls, under the same assumptions as above, provides 92% power to detect a univariate biomarker with a MFC of 1.5 between SMA and control cases (t-test) when the FDR is controlled at level 0.05.

- 1. Statistical Analysis

The primary outcome for this study is the Modified Hammersmith Functional Motor Scale. A score of “0” is acceptable for those unable to perform any of the measurements (e.g., type I SMA subjects). Secondary outcomes include SMA type, timing of symptoms (age of disease onset, age of maximum function), motor milestones, nutritional assessment (height, weight, triceps skin fold thickness, ulnar length, nutritional question), pulmonary assessment (standardized question about level of respiratory support, FVC when ≥ 5 years), SMN protein, SMN transcript and SMN2 copy number. Descriptive statistics (e.g., means, standard deviations, percents) of all outcomes will be calculated for SMA and control cases, as well as by SMA type. The populations will also be described by vital signs, loss of motor function, and age appropriate neurological exam results.

In order to find disease-specific biomarkers, comparison of biomarkers between SMA and control cases will be performed using regression analysis, controlling for sex and age. Correlations of biomarkers with outcomes will be conducted within SMA cases, as well as in the combined population of SMA and control cases.

To model the correlation of each individual biomarker with the Modified Hammersmith Functional Motor Scale, univariate regression analyses will be performed, controlling for sex and age. Additionally, elastic net multivariate regression (25) will be used to find a composite set of biomarkers that correlates with outcome.

Univariate regression and elastic net multivariate regression will also be used for continuous secondary outcomes (e.g., age of disease onset, height, weight). For categorical outcomes (e.g., SMA type), analysis of variance (ANOVA), controlling for sex and age, will be performed to discover individual biomarkers that vary by outcome. Likewise, PAM (Prediction Analysis of microarrays) (26) will be used to try to find a composite set of biomarkers that varies by outcome.

In all analyses a p-value ≤ 0.05 will be considered statistically significant. The false discovery rate (27) will also be controlled. If there is an extensive amount of missing data, or data appears not to be missing completely at random, then multiple imputations will be considered. Standard statistical software packages (e.g., SAS) will be used.

- 1. Interim Analysis

No interim analysis for safety or efficacy will be performed during this study.

- 1. Potential Risks and Benefits

Potential risks to study subjects are minimal. Blood will be drawn in volumes that are approximately half (or less than half) of the maximum blood draw allowed for children (by weight) (28) (29). SMN2 copy number will be genotyped from DNA specimens for all cohorts. SMN1 gene analysis will only be done on those control subjects with no genetic relationship to SMA children. SMA subjects will be pre-diagnosed and therefore no further risks are anticipated from a genetic point of view. The control subjects may opt out of the DNA portion (SMN1 gene analysis) of the study. The control subject’s risk is that the study does not benefit the individual directly.

Potential benefits are that study subjects will benefit from the satisfaction that they are participating and contributing to SMA research.

The risk/benefit ratio is favorable since participation in the study is reasonably commensurate to routine care for an SMA subject over the course of one visit.

- 1. Limitations of the Study

Several limitations were considered in the design of the study.  Outlined below is how the study proposes to mitigate these limitations:

1. Biomarkers may vary by age and Type I subjects will be on the younger end of the age distribution.  The proposed solution is to control for age in all statistical models.
2. Based on the inclusion criterion for age, the study outcomes may not be generalization to children <2 or >12 years old. The primary outcome is not reliable in children less than 2 years of age. Any putative biomarkers identified in this effort would need to be validated in follow-on studies in a broader age distribution.
3. The sample size selected is based on number of specimens collected and it is possible that less than 100% of specimens collected will be analyzable. The study will allow for replacement of subjects to account for these specimens.
4. There is a potential that differences in standards of care between centers or regional differences (in diet or lifestyle) may have an impact on putative biomarker levels  It is unknown whether this has an effect prior to identification of a biomarker.  An ideal biomarker would be robust against effects of lifestyle and diet. The study design attempts to mitigate this potential effect by instituting site caps by cohort.
5. Recruitment of control children may be difficult as they do not have a direct or indirect benefit (other than siblings) from the study.  It is possible that this will be an issue; however the pool of control children is significantly larger than the SMA pool and therefore 20 control individuals is achievable.

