**RATIONALE FOR NUMBER OF SUBJECTS**

- The number of subjects was selected based on clinical and statistical considerations.
- The sample size for the SMA subjects was selected to achieve 83% power for the primary outcome of Modified Hammersmith Functional Motor Scale, using an elastic net regression analysis, assuming a 0.75 correlation between the observed and theoretical outcomes. The power estimate is based on an average of 100 simulated datasets using data available from the original Hammersmith Scale.
- The sample size of 20 control subjects was selected to achieve at least 90% power to detect a univariate biomarker with a mean-fold change (MFC) of 1.5 when the false discovery rate is controlled at 0.05.
- In both power calculations it was assumed that 10% of profiled analytes are true biomarkers, and that variance of analytes is equal to 0.2.

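### The 92% power for SMA versus controls and the 89% ANOVA power are said to share one set of assumptions, but no scale tried gives both, and the scale is not stated

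*Protocol*

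**What the plan says.** Protocol section 11.1 (Power Calculations) gives three linked statements.

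- The primary power calculation sets the common inputs: it "assumes that 10% of analytes are true biomarkers", with "a variance of 0.2 for all analytes, with 100 analytes profiled".
- For SMA type, at an MFC of 1.3 and under those assumptions, the power "is 89% for univariate analysis of variance (ANOVA), when the false discovery rate (FDR) is controlled at level 0.10". The type differences are taken as monotone and identical, and the figure averages 100 simulated datasets.
- The control comparison carries those inputs over; its basis is "the sample size of 100 SMA cases and 20 controls, under the same assumptions as above". The result claimed for this design is that it "provides 92% power to detect a univariate biomarker with a MFC of 1.5 between SMA and control cases (t-test", with the FDR held to 0.05.

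The synopsis (Rationale for Number of Subjects) rests the control group on the last figure: "The sample size of 20 control subjects was selected to achieve at least 90% power to detect a univariate biomarker". It repeats the 10% share of true biomarkers and the variance of 0.2.

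Neither place says whether the fold change and the variance are on a natural-log, log2 or untransformed scale. The sidedness, the t-test version (pooled or Welch) and the FDR procedure are not given either.

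**The concern.** The ANOVA and t-test figures use the same variance, number of analytes and share of true biomarkers, so one can be checked against the other. The ANOVA shows which scale is plausible, and on that scale the t-test falls well short of 92%.

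The 92%, or at least 90% in the synopsis, is the only quantitative basis given for 20 controls. If the natural-log scale is the intended one, about 20–22% of true disease markers of the planning size would be missed, against the 8% that the stated figure implies.

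**Working it through.** **Inputs from section 11.1.** t-test: n = 100 and 20, MFC 1.5, FDR 0.05. ANOVA: n = 15, 45 and 40, equal steps of MFC 1.3, FDR 0.10. Both: variance 0.2, 10 of 100 analytes true. **Assumed, because not stated:** the scale, normal analytes, Benjamini-Hochberg (BH) control or BH adjusted for the share of true nulls, and a reference mean of 1 on the untransformed scale. Power is the average over the true biomarkers.

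**Formulas.**
- t-test noncentrality: δ / √(0.2 × (1/100 + 1/20)) = δ / √(0.2 × 0.06) = δ / 0.1095, with 118 df.
- ANOVA noncentrality: λ = S d² / 0.2. With type means 0, d and 2d the weighted mean is 1.25d, so S = 15(1.25²) + 45(0.25²) + 40(0.75²) = 48.75.
- Per-test level α under BH: α = FDR × (0.9α + 0.1 × power), solved jointly with the power.

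**Natural log.**
- t-test: δ = ln 1.5 = 0.405, noncentrality 3.70, α = 0.0041, power 77.8%. Adjusting BH for the true-null share gives α = 0.0046 and 79.0%.
- ANOVA: d = ln 1.3 = 0.262, λ = 48.75 × 0.0688 / 0.2 = 16.8, power 86.2%; adjusted, 87.2%.

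**All three scales**, by simulation of up to 2,500 datasets (ranges cover the FDR variants):

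| Scale | t-test, pooled | t-test, Welch | ANOVA, classical | ANOVA, Welch |
|---|---|---|---|---|
| Natural log | 78–79% | 70–72% | 86–87% | 83% |
| Untransformed (differences 0.5 and 0.3) | 95–96% | 92–93% | 95.5–96% | 94% |
| log2 | 99% | 98–99% | 99.9% | 99.8% |
| **Protocol** | **92%** | | **89%** | |

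All t-tests in the table are two-sided. A one-sided test on the natural-log scale gives about 85–86%. The 92% can be reproduced in one cell, untransformed with Welch, but that row misses the 89% by 5 points or more.

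**Check that needs no choice of log base or variance.** On a log scale both noncentralities scale with (log base)²/variance, so their ratio is fixed: (t noncentrality)² / λ = (0.1644 / 0.06) / (48.75 × 0.0688) = 2.740 / 3.356 = 0.817.
- ANOVA at 89% needs λ ≈ 17.87. The t noncentrality is then √(0.817 × 17.87) = 3.82, and the power is 81–82%.
- t-test at 92% needs a noncentrality of about 4.30. Then λ = 4.30² / 0.817 ≈ 22.6, and the ANOVA power is about 96%.

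**What 92% would take on the natural-log scale.** An MFC of 1.6 gives 92% with 20 controls (91.9% by formula, 92.4% by simulation).

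**Simulation error.** An average over 100 datasets has a standard error of about 1.5 points for the t-test on the natural-log scale. A gap of at least 12 points (92 − 80) is then about 8 standard errors. The protocol gives no dataset count for the t-test, so 100 is an assumption here.

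**The case against.** A reader might infer that the protocol's inputs by themselves give 78%, so that 92% is an arithmetic slip. The documents do not support that. The scale is missing, and across the readings tried the t-test power runs from about 70% to 99%. Two of the three scales meet the synopsis's 90%, and the untransformed Welch reading lands on 92%. The natural-log scale is an inference from the ANOVA figure. The stated PAM accuracy of 61% adds little to it: natural log gives about 62% only if an equal-prior rule is scored on the 15/45/40 mix, and 65–66% under other scorings.

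The fixed ratio also holds for log scales only. On the untransformed scale it is (0.25 / 0.06) / (48.75 × 0.09) = 0.950. If the reference mean is left free instead of set to 1, an ANOVA at 89% gives a t noncentrality of √(0.950 × 17.87) = 4.12 and a pooled two-sided power of about 89%. That narrows the gap to about 3 points, but needs a reference mean near 0.9 that the protocol does not mention.

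Nor does the check show that the 89% should be changed. On the natural-log scale the adjusted ANOVA value is about 87%, and 100 datasets carry a standard error of about 1.2 points, so 89% is about within simulation error.

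All of this stands. It limits the point to a conflict between two printed figures and an unstated scale. It does not remove the conflict, because the t-test figure is expressly tied to the assumptions behind the ANOVA figure.

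**Conclusion.** The point holds as an inconsistency. With variance 0.2 and the readings tried, no single scale gives both 89% and 92%. On the scale that best fits the ANOVA figure, natural log, the two-sided pooled t-test has about 78–80% power (about 70% with Welch, about 85% one-sided), which is 12 to 14 points below the stated 92% and below the synopsis's 90%. This rests on normal analytes, average power over the true biomarkers, BH-type FDR control and, for the untransformed scale, a reference mean of 1.

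It does not follow that 20 controls are too few or that the ANOVA figure is wrong. Severity is moderate: the comparison with controls is a secondary objective of a single-visit, non-interventional pilot study whose candidate markers are to be verified in later studies.

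**What to change.** Re-run the t-test calculation on the same scale and assumptions as the ANOVA. In section 11.1 state the scale of the fold change and variance, the sidedness, the t-test version and the FDR procedure. Restate the result in section 11.1 and in the synopsis so that they agree. If the natural-log scale is confirmed, that means about 78–80% power at an MFC of 1.5, or about 92% at an MFC near 1.6. Remove the synopsis's claim of at least 90% unless the re-run supports it. Keep 20 controls, and leave the 89% for the ANOVA unless the re-run changes it.

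The cost is one short simulation and a few sentences in two places. No subjects, visits or analyses change. The stated power may become less favourable.

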# STUDY MEasurements

- 1. Motor Function Assessment

The Modified Hammersmith Functional Motor Scale (15) provides a tool for evaluation of motor function in pediatric subjects with SMA type II and type III. The Modified Hammersmith Functional Motor Scale will be performed according to the Study Manual of Operations. A score of “0” is acceptable for those unable to perform any of the measurements (e.g., type I SMA subjects). In this study, both control subjects and SMA subjects will undergo the assessment as the scale is being used as the primary outcome. A minimal amount of equipment is required to perform the evaluation and the total duration is ~20 to 30 minutes to complete. Each site will have a clinically trained person performing these evaluations. It is anticipated that for control subjects, the assessment will require a minimum amount of effort and will take approximately 10 minutes to complete.

- 1. 10-meter Timed Walk Test

A 10-meter Timed Walk Test will be performed on all ambulatory SMA subjects and controls according to the Study Manual of Operations. This test compares higher functioning subjects with SMA and control subjects in their ability to walk 10 meters. (16, 17, 18)

- 1. Pulmonary Function

On subjects age >5 years, spirometry will be performed according to the Manual of Operations to measure the maximal volume of air forcibly exhaled from the point of maximal inhalation (forced vital capacity, FVC). The test will be performed 3 times in a sitting position. Subjects unable to sit may perform the FVC in a supine position and document on the appropriate CRF. Subjects who are unable to perform or complete the FVC tests may still participate in the study.

- 1. Triceps Skin Fold Thickness

The measurement of skin fold thickness of the subject’s upper arm will give an estimate of body composition and will be correlated with BMI Z score. Variability of measurement will be decreased by detailed standard procedures in the Manual of Operations and hands-on training.

- 1. Height, Weight and Ulnar Length

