To calculate the BMI Z score (refer to 7.5) a subject’s height and weight is measured. Height will be measured to the nearest centimeter or tenth of an inch; weight will be measured to the nearest tenth of a pound or nearest gram. The subject is to wear light clothing with socks and shoes removed. Ulnar length will be measured because height measurement may be unreliable when neuromuscular weakness or spinal deformity is present (19). Ulnar length will be measured to the nearest centimeter or tenth of an inch as the distance between the proximal end of the ulna and the tip of the styled process. Detailed standard procedures for all these measurements are in the Manual of Operations.

- 1. BMI Z Score

The BMI Z Scale (20) is used to determine a child’s body mass index (BMI). The BMI-percentile-for-age calculator automatically adjusts for differences in height, age and gender, making it is one of the best tools for evaluating a growing child's weight. Many SMA children have a higher average BMI related to their lack of motor activity. The BMI Z Score will be automatically calculated in the Data Management System (ADEPT) upon data entering the height, weight, and ulnar length.

- 1. Specimen Collection

Up to approximately 10-mL sample of blood will be collected for gene expression (mRNA), proteomic and metabolomic analysis. All samples will be shipped and stored at the central laboratory until the end of the study where they will be shipped to the designated genomic laboratory (DNA and mRNA samples) and biomarker laboratory (plasma) for analysis. From the blood, DNA will be extracted to determine SMN2 copy number and SMN1 genotype (for genetically unrelated controls only). Please refer to the Manual of Operations for detailed processing and shipping instructions.

Up to 10-mL sample of urine will be collected for proteomic and metabolomic analysis. All samples will be shipped and stored at the central laboratory until the end of the study where they will be shipped to the designated biomarker laboratory for analysis. Please refer to the Manual of Operations for detailed processing and shipping instructions.

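### The BMI Z score that height and weight are collected to produce is missing from the nutritional outcomes in 11.2, and height and weight modelled separately do not measure weight for height

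*Protocol*

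**What the plan says.** Protocol 7.5 gives the reason for the two measurements: "To calculate the BMI Z score (refer to 7.5) a subject’s height and weight is measured". Section 7.6 adds that "The BMI Z Score will be automatically calculated in the Data Management System (ADEPT" system once height, weight and ulnar length are entered. It says the age-based BMI calculator "automatically adjusts for differences in height, age and gender, making it is one of the best tools for evaluating a growing child's weight". The only analysis described for the score is in 7.4, where skin fold thickness "will give an estimate of body composition and will be correlated with BMI Z score".

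Section 11.2 lists the nutritional secondary outcomes as "nutritional assessment (height, weight, triceps skin fold thickness, ulnar length, nutritional question". It then says that univariate regression and elastic net "will also be used for continuous secondary outcomes (e.g., age of disease onset, height, weight". BMI Z score is named nowhere in 11.2.

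On adjustment, 11.2 states control for sex and age in the SMA-control comparison, the univariate motor-scale regressions and the ANOVA for categorical outcomes. It does not repeat this for continuous secondary outcomes or say how age enters the elastic net. Section 11.5 proposes age control in all statistical models, because biomarkers may vary with age and type I children will be younger.

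**The concern.** One secondary objective is to find markers that correlate with nutritional assessment. The protocol collects two inputs in order to form an index of weight relative to height, age and sex, then models the inputs one at a time and leaves the index out of the outcome list.

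Age adjustment turns raw height into roughly height for age, and raw weight into roughly weight for age. The first is stature. The second combines stature with weight for height. A marker of over- or undernutrition could therefore be missed against height and diluted against weight, while a marker of short or tall stature could be reported as nutritional through weight. At stake is how one secondary objective of an exploratory pilot is interpreted.

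**Working it through.** No figure in the protocol depends on this choice, so there is none to reproduce. The check has two steps. Growth rates and spreads are not in the protocol; they are assumptions, shown as ranges.

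**Step 1. How much of raw height and weight is age, and does adjustment deal with it?**

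Share of variance due to age = (slope × SD of age)² / [(slope × SD of age)² + (within-age SD)²]. The age range of 2 to 12 years inclusive is taken as uniform over 10 or 11 years.

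- Worked case for height, with 6 cm/year and within-age SD 6 cm: SD of age = 11/√12 = 3.18; (6 × 3.18)² = 363; 363/(363 + 36) = 0.91.
- Height range (5-7 cm/year, SD 4-10 cm): 68-97%.
- Weight range (2-3 kg/year, SD 3-9 kg): 29-91%.

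Raw height is mostly age throughout. For weight this depends on the assumed spread.

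Next, a marker that tracks age but has no link to nutrition was simulated (n = 100, the planned 15 + 45 + 40 SMA children; 1,500 runs per setting). The table gives the percentage of runs with p < 0.05.

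| Marker's correlation with age | Height, no age term | Weight, no age term | Either outcome, linear age in model |
|---|---|---|---|
| 0.1 | 17% | 13% | about 5% |
| 0.2 | 49% | 42% | about 5% |
| 0.3 | 84% | 77% | 4-5.5% |
| 0.5 | 100% | 99% | 4.5-5.5% |

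Age control as stated in 11.5 therefore returns the error rate to nominal in these regressions.

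**Step 2. With age in the model, what do height and weight measure?**

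Since weight = BMI × height², log weight = log BMI + 2 × log height. At a given age, if BMI and stature vary independently (an assumption), the stature share of the variance of log weight is (2 × CV of height)² / [(2 × CV of height)² + (CV of BMI)²].

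Take height 86 cm at age 2, growth 6 cm/year and within-age SD 6 cm. At the mid-age of 7.5, height is 86 + 6 × 5.5 = 119 cm, so 2 × 6/119 = 0.101, whose square is 0.0102.

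- BMI CV 0.12: 0.0102/(0.0102 + 0.0144) = 41% of age-adjusted weight variance is stature.
- BMI CV 0.25: 0.0102/(0.0102 + 0.0625) = 14%.

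A marker with correlation 0.3-0.4 with stature and none with BMI then has an expected correlation with age-adjusted weight of between 0.3 × √0.14 = 0.11 and 0.4 × √0.41 = 0.26. A marker with correlation 0.3-0.4 with BMI for age has between 0.3 × √0.59 = 0.23 and 0.4 × √0.86 = 0.37 with weight, and zero with height.

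Simulated detection at p < 0.05 (n = 100, 2,000 runs, linear age in every model, 6 cm/year, BMI CV 0.12-0.25, marker correlation 0.3-0.4):

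| Marker | vs height | vs weight | vs BMI Z |
|---|---|---|---|
| True BMI-for-age marker | 4-6% | 60-96% | 86-99% |
| Stature only, no link to BMI | not tabulated (height is stature) | 16-64% | 4-6% |

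A separate run under other assumed spreads gave 73-89% for weight and about 95% for BMI Z with the true BMI marker, and 23-56% for weight with the stature-only marker. The pattern is the same. These runs cover univariate regression only, and they take height as measured without error, which favours BMI Z.

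**The case against.** A reader might infer that the nutritional analysis will mainly return markers of age, which would then pass for severity markers because type I children are younger. The document does not support this. Section 11.5 commits to age control in all models, and step 1 shows that this removes the spurious association. What stands is narrower: 11.2 does not carry the commitment through to the continuous secondary outcomes or the elastic net. It is also not established that raw weight is mostly age.

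A reader might also infer that BMI Z has been deliberately excluded, or that nutrition is judged on height and weight alone. Neither follows. The secondary outcomes are introduced by a word that leaves the list open, height and weight are given as examples, and skin fold thickness, ulnar length and a food-intake question are listed too. The choice of derived variables can be left to a SAP. Against that, the protocol itself enumerates the nutritional measures and names raw height and weight as modelled outcomes, while 7.5 and 7.6 present the score as the purpose of measuring them. That mismatch lies within the protocol.

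The strongest objection concerns replacing height and weight with BMI Z. Section 7.5 warns that height may be unreliable with weakness or spinal deformity, and BMI Z inherits that error. Section 7.6 links higher BMI in SMA to lack of motor activity, so BMI Z may itself track severity. Both points stand. They argue for adding the score beside the other measures, not for leaving it out.

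**Conclusion.** The point holds as a minor inconsistency with a practical consequence. The protocol measures height and weight to form BMI Z, has the score computed automatically, and does not name it among the outcomes to be related to biomarkers. With age controlled, height carries no weight-for-height signal (detection at chance, 4-6%). Weight carries a diluted one and also flags stature-only markers in 16-64% of runs.

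These sizes rest on assumed growth, BMI spread and marker correlations, on BMI being independent of stature at a given age, and on error-free height. The direction follows from weight being BMI times height squared; the exact percentages should not be relied on. The primary outcome, the sample size and the stated power are unaffected.

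**What to change.** In section 11.2:

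1. Add BMI Z score to the nutritional outcomes, for both the univariate and the elastic net models.
2. Keep height, weight and ulnar length, either as descriptive variables or as outcomes that are always age- and sex-adjusted. Keep skin fold thickness and the nutritional question as they are.
3. State that the age control of 11.5, together with sex, applies to the continuous secondary outcomes, and that age and sex enter the elastic net as unpenalised covariates.

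The cost is a few edited lines. No new data are needed, because the score is already computed. The downsides are one more secondary outcome under false discovery rate control, and a score that shares the height unreliability noted in 7.5. For that reason it should be read alongside skin fold thickness and the other measures and should not replace them.

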# Trial Enrollment

There is no randomization or blinding protocol for this study as there is no therapeutic intervention.

- 1. Screening Procedures

The Principal Investigator at each clinic site (or designee) and the study coordinator will have responsibility for subject recruitment including a chart review to identify potentially eligible subjects. All screening must comply with the local institution’s Health Insurance Portability and Accountability Act (HIPAA) requirements. Subjects may be screened for eligibility more than once during the accrual period.

- 1. Subject Enrollment and Site Enrollment caps

Subjects will be enrolled based on the definitions listed under inclusion and exclusion criteria. As treatment patterns differ between institutions, the study aims for a broad recruitment over a number of sites rather than 1 or 2 sites dominating the subject pool. This aim is balanced by the logistical concern of not significantly hampering recruitment in a rare disease. Subject caps will be lifted 3 months after the first subject is enrolled in the study. To enable recruitment to proceed smoothly, sites will be able to access real-time recruitment information by cohort via the web through the data management system (ADEPT). The distributions of sex and age of SMA cases will be monitored regularly, and the plan for recruitment of controls of appropriate sex and ages may be altered in order to match distributions.

The following subjects caps (maximum number of subjects allowed per site) for each cohort are defined below:

Table 1: Subject Caps Per Site

|  | Total subjects | Subject Cap per site |
| --- | --- | --- |
| Type I | 15 | 5 |
| Type II | 45 | 10 |
| Type III | 40 | 10 |
| Controls | 20 | 7 |
| TOTAL | 120 |  |

- 1. Replacement of Subjects

Subjects may be replaced by additional subjects in the same cohort prior to the close of the enrollment period if:

- Subject’s specimen(s) collected are lost in transit.
- Subject’s specimen(s) are broken upon receipt.
- Subject’s specimen(s) are compromised or unanalyzable (i.e. hemolyzed) upon receipt.
- Specimens of a particular type do not meet minimum volumes for processing.
- No specimens of a particular type are collected during the visit.
- Study assessments required for the primary or secondary outcome are not collected.

Any clinical data collected or usable specimens for the subjects replaced may be analyzed and used in the statistical analysis.

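### The SMA-versus-control regression in section 11.2 leaves out SMA type, so for markers that differ by type the test is conservative and gives up a few points of power that could be recovered almost for free.

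*Protocol*

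**What the plan says.** - **Analysis.** Protocol section 11.2 states that "comparison of biomarkers between SMA and control cases will be performed using regression analysis, controlling for sex and age". SMA type is not among the covariates. It is examined in a separate ANOVA and a PAM analysis.
- **Recruitment.** Sections 4 and 11.1 fix the SMA group as three cohorts: "A sample size of 15 Type I, 45 Type II, and 40 Type III SMA cases".
- **Assumed type effects.** Section 11.1 powers the type comparison for a mean fold change of 1.3 (ANOVA) or 1.2 (PAM) and adds: "These power calculations assume monotone identical differences between SMA types".
- **Sizing of the control comparison.** Section 11.1 says that a "sample size of 100 SMA cases and 20 controls, under the same assumptions as above, provides 92% power" for an "MFC of 1.5 between SMA and control cases (t-test) when the FDR is controlled at level 0.05". The shared assumptions are "10% of analytes are true biomarkers, a variance of 0.2 for all analytes, with 100 analytes profiled".
- **Markers of interest.** Section 2.2 takes the identified candidate markers into the control comparison. Under the primary objective, these are markers that track severity.
- **Age.** Section 11.5 expects type I children to be younger and relies on age adjustment in all models.

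**The concern.** The markers that matter most in the control comparison are those that rise or fall with severity, and under section 11.1 these differ by type. A two-group comparison adjusted for sex and age alone counts those differences as random scatter. They are not sampling error when the type mix is set by quota. The inflated residual variance is also applied to the mean of only 20 controls, who have no type spread, and that mean carries most of the standard error. A true severity marker is therefore somewhat less likely to be confirmed as disease-associated, and the loss grows with the size of the type gradient.

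**Working it through.** **Inputs from section 11.1.** 100 SMA (15/45/40) and 20 controls; variance 0.2; 10 of 100 analytes true; SMA-versus-control fold change 1.5; FDR 0.05; type fold change 1.3 with equal steps.

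**Assumptions, not stated in the protocol.** Natural-log scale, two-sided test, Benjamini-Hochberg procedure, 1.3 as the step between adjacent types, and 0.2 as the within-type variance.

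**1. The plan's own figure.** With no type differences, SE = √(0.2 × (1/100 + 1/20)) = √0.012 = 0.1095, and ln 1.5 / SE = 0.4055 / 0.1095 = 3.70. The per-test level a solves a = 0.05 × (0.9a + 0.1 × power), so a = 0.005 × power / 0.955. This gives a = 0.0041 and power 78%, not the stated 92%. A one-sided test gives 85 to 86%, log2 gives 99% and a raw difference of 0.5 gives 95%. None of these reproduces 92%. The stated 89% for the ANOVA is approached most closely on the natural-log scale (86 to 87%), which is why that scale is used as the base case.

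**2. Variance added by type.** Score the types 0, 1, 2 with weights 0.15, 0.45, 0.40. Mean = 0.45 + 0.80 = 1.25; mean square = 0.45 + 1.60 = 2.05; variance = 2.05 − 1.25² = 0.4875. With 1.3-fold steps, the between-type variance is 0.4875 × (ln 1.3)² = 0.4875 × 0.0688 = 0.0336.

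**3. Residual variance without type.** (99 × 0.2 + 100 × 0.0336 + 19 × 0.2) / 118 = 0.228.

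**4. Effect on the standard error.** The estimated SE is √(0.228 × 0.06) = 0.117. With the mix fixed, the true SE is still 0.1095, so the estimate is too large by a factor √(0.228/0.2) = 1.07. Most of the excess sits on the controls: 0.228/20 = 0.0114 instead of 0.0100, against 0.00228 instead of 0.00200 for SMA.

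**5. Effect on the test.** Under no average difference, the nominal 5% critical value 1.98 acts like 1.98 × 1.07 = 2.12, a true level of about 3.4%. Simulation gives 3.5 to 3.6%, against 4.7 to 5.0% with type in the model. For power, Φ((3.46 − t) × 1.07), with t the two-sided critical value at level a and a re-solved to 0.0037, gives 70%.

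**6. With type in the model.** The contrast weighted 0.15/0.45/0.40 has variance 0.2 × (0.15²/15 + 0.45²/45 + 0.40²/40) + 0.2/20 = 0.002 + 0.010 = 0.012. This is the SE of step 1, so power returns to about 77 to 78%.

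**7. Scenarios** (1.3-fold steps and natural log unless noted):

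| Scenario | Without type | With type | Loss (points) |
|---|---|---|---|
| No type differences | 77% | 77% | 0 |
| 1.2-fold steps | 73% | 77% | 3–4 |
| 1.3-fold steps | 70% | 77% | about 7 |
| 1.3-fold steps, type I younger | 72% | 76–77% | 4–5 |
| Effect set near 92% | 87–89% | 91–92% | 3–4 |
| log2 scale | 97.9% | 99.4% | 1.5 |

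Repeat simulations of the 1.3-fold case ranged from 68 to 71% without type and 76 to 78% with it. Realised FDR was about 0.04 to 0.05 under both models.

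**8. If 0.2 is a total variance.** The within-type variance is then 0.2 − 0.0336 = 0.166. Simulated power is 80.1% without type and 86.5% with it, so the analysis still loses about 6 points.

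**The case against.** Four points can be made for the plan as written.

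- **Nothing is invalid.** The planned test errs on the cautious side and its FDR is controlled. This is one secondary analysis in a discovery pilot whose candidates need later validation. That stands, and it limits the matter to efficiency.
- **Other analyses exist.** Section 11.2 also correlates markers with outcomes in SMA and controls combined, and analyses type by ANOVA and PAM. A severity marker therefore has other routes to detection. This stands too, but it does not restore the power lost in the control comparison.
- **The SAP may add detail.** Group coding is often settled there, and the SAP is not at hand. However, the protocol itself names the covariates for this comparison, and type is not one of them.
- **The target is not defined.** The SE is too large for the mean at the enrolled type mix, and the protocol does not say that this is the target. It is, however, the quantity that a plain SMA-minus-control comparison estimates. Replacement under section 5.3 stays within cohort, but data from replaced subjects may still be used, so enrolled proportions can drift slightly from quota. The weights should follow enrolment.

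A reader might also infer that the stated 92% is too high because the sizing ignored type. The document does not support this. It gives "a variance of 0.2 for all analytes" without saying whether that is within type or total. The failure to reproduce 92% is a separate matter. Nor do the site caps in section 5.2 fix the type mix: they limit each site and are lifted after three months. The mix comes from the cohort totals.

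**Conclusion.** The point holds as an efficiency loss that can be avoided, confined to markers that differ by type. At 1.3-fold steps between adjacent types the loss runs from about 1.5 to 7 points. The upper figure needs the natural-log scale, variance 0.2 within type, two-sided Benjamini-Hochberg control at 0.05 and no link between age and type. Section 11.5 expects such a link, which brings the loss to about 4 to 5 points.

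A flat statement that 7 points are lost would go beyond the document, because scale, sidedness and the meaning of 0.2 are not given. The 7 points are also measured from a recomputed 77%, not from the stated 92%. It would likewise be too strong to say that true severity markers fail the comparison, since about 70% of them still pass in the 1.3-fold case. Whether the sizing ignored type differences cannot be settled from the protocol, but the analysis loses power on either reading of 0.2.

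**What to change.** In section 11.2, specify the SMA-versus-control regression with indicators for type I, type II, type III and control, plus sex and age. Test the average SMA-minus-control contrast with weights equal to the enrolled type proportions (planned 0.15, 0.45 and 0.40). The contrast must be written out, because control children have no SMA type. It addresses the same overall question, and the three type-specific differences from control come from the same fit.

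In section 11.1, add a clause saying whether 0.2 is a within-type or a total variance, and on which scale.

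The cost is one sentence, one contrast statement per analyte and two residual degrees of freedom (116 to 114). Type is already recorded for every SMA child, and essentially nothing is lost for markers that do not differ by type.
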